### Study population

The WEBAPPAC study addresses breast cancer patient candidates to initiate an adjuvant hormone therapy. Eligibility criteria are presented in Table 1.

**Table 1 Tab1:** Eligibility criteria in the WEBAPPAC study

Inclusion criteria	Non-inclusion criteria
• Patient aged ≥ 18 years • Breast cancer patient candidate for adjuvant hormone therapy • Proficiency in French language • Patient with a cell phone and an Internet connection • Patient able to use a computer, smartphone, or tablet. • Patient affiliated to a social security system	• Patient who has previously received hormone therapy for cancer. • Patient not trained in the use of the application • Any medical or psychiatric condition that might compromise the patient’s ability to participate in the study • Patients with locoregional or metastatic recurrence • History of other cancer. • Patient deprived of liberty, under guardianship or curatorship • Simultaneous participation in a therapeutic clinical trial or other clinical study involving a connected tool • Patient unable to undergo trial follow-up for geographical, social or psychopathological reasons

### Study site

The study is conducted in the comprehensive cancer centre François Baclesse, as indicated on https://www.clinicaltrials.gov/ct2/show/NCT04554927.

### Study experimental plan

The study will be proposed by breast nurses or physician oncologists to patients who meet the eligibility criteria. An explanation of the study and an information note will be given to them. Patients will be enrolled in the study once provided their written informed consent. Then, the randomization will be performed on the eCRF portal, stratified on the type of hormone therapy (Aromatase Inhibitor (AI) or Tamoxifen), as these treatments differ in terms of patients’ age at prescription, tolerance profile and adherence difficulties.

Patients will be assigned, according to a 1:1 randomization, to one of the following arms:

Experimental arm: WEBAPPAC web-application support (WEBAPPAC arm).Control arm: standard support.

The patients will be recruited over 30 months. Their participation will last 18 months.

### Modalities of participation

All enrolled patients will be given an adherence notebook and be instructed to complete it as well as asked to bring her hormone therapy prescription to each visit to the Center.

#### Control arm: standard support only

During the end of active treatment consultation, the oncologist will prescribe the adjuvant hormone therapy treatment in accordance with multidisciplinary team decision and patient.

The SCP will be then given to the patient, presented as a personalized follow-up and medical monitoring program alternating with her general practitioner. The relay with the attending physician will be carried out. The oncologist will then receive patients in consultation at 6 and 18 months after the start of hormone therapy. The patient will be free to discuss any concerns she may have with her attending physician. Information on social and psychological support for the patient or her family will be provided by the breast nurses at the end-of-treatment consultation, supplemented by a brochure entitled “Preparing for Life After Treatment”.

The breast nurse who has accompanied the patient throughout her care will remain available by phone or email if necessary.

#### Experimental arm: standard support plus WEBAPPAC web-application

Patients randomized in the experimental arm will receive information in the same way as patients in the standard arm, and will be planned the same number of appointments at the center.

The web-application will be installed on the patients’ smartphone after randomization, and links to install it on other devices will be sent them by email with instructions. Patients will be trained on the devices by breast nurses immediately after the randomization, a help paper booklet will be given to them and will be also available online.

A phone call will be made 15 days after this training to check the patient’s ability to master the tool.

The patient will be free to log in the web-application at any time to get advice, recommendations and to track her side effects. In addition, the patient will be sent a notification every 15 days for the first 3 months, and then once a month to invite her to report any symptoms (fatigue, anxiety, pain, presence and intensity of hot flashes and sexual problems).

As part of the protocol, patients will be reminded (via SMS, and/or email) to complete Patient-Reported Outcomes via the web-application:

6 weeks and 3 months after hormone therapy start.one week before the consultation with the oncologist, planned 6 and 18 months after the hormone therapy start.

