**Fig. 1 Fig1:**
[figure not shown]
A graduated immediate response adapted to the patient through the WEBAPPAC web-application

Besides this personalized monitoring, the web-application is intended to improve the management of ADRs induced by hormone therapy, by:

Providing health and dietary advices (physical activities and sports, practical advice, “take care of yourself” advice cards, cooking recipes, etc.)Providing information that will allow patients to apply symptomatic treatments without a prescription in close collaboration with their pharmacist (lubricant, level 1 analgesic, etc.)Referring patients to primary health care professionals (attending physician), organizations and structures adapted to their needs (sports educators, social workers, dieticians, patient associations, etc.).Alerting the nurse accompanying the patient on the breast cancer treatment pathway in the event of non-adherence with the hormone therapy treatment.

However, it is to notice that this device should not be considered as an emergency alert.

In this context, we implemented the WEBAPPAC study, herein presented. To our knowledge, this randomized study is the first one, to date, aiming to evaluate the effectiveness of using a web-application on adherence to adjuvant hormone therapy among breast cancer patients with breast cancer.

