### Primary outcome

The main objective is to evaluate the benefit of the WEBAPPAC web-application on patient adherence to adjuvant hormone therapy for breast cancer 18 months after treatment start.

The primary endpoint of the study is the proportion of patients with adherence failure of hormone therapy within 18 months after treatment start, in each arm. Adherence failure of hormone therapy will be defined by at least one of the following items:

Adherence score less than 6 on the 8-item Morisky questionnaire (MMSA8) [22–25], completed at 18 months;Treatment discontinuation since at least one month, documented in the patient’s adherence notebook;Absence of hormone therapy dispensation for at least one month, documented on the hormone therapy prescription, with traceability of each dispensation noted on the prescription;Permanent discontinuation of hormone therapy as declared by the patient at the 18-month follow-up medical consultation.

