### Study assessments

The overview of study assessments and procedures is detailed in Table 2.

**Table 2 Tab2:** Overview of study assessments in the WEBAPPAC study

TIME Point	Before inclusion	Inclusion and randomisation ^a^	Day 15^b^	6 Week^b^	3-months^b^	6-months^a^	18-months ^a^
		Visit 1				Visit 2	Visit 3
Informed consent	•	•^a^					
**Training of the patient in the Web application**		**•** ^**b**^					
**Medical examination** (medical history, weight, height, vital parameters)		**•** ^**a**^					
**Quality of life self-report questionnaires (EORTC QLQ C30; and QLQ BR23)**		**•** ^**a**^				**•** ^**a**^	**•** ^**a**^
**Anxiety and Depression Questionnaire (HADS)**		**•** ^**a**^				**•** ^**a**^	**•** ^**a**^
**Assessment of pain using the Visual Analogue Scale (VAS)**				**•** ^**b**^	**•** ^**b**^	**•** ^**a**^	**•** ^**a**^
**Pain score (BPI)**		**•** ^**a**^					**•** ^**a**^
**Morisky Medication Adherence Scale (MMAS8)**				**•** ^**b**^	**•** ^**b**^	**•** ^**a**^	**•** ^**a**^
**Measurement of user experience (self-questionnaire (SUS))**							**•** ^**b**^
**Phone call** to ensure that there are no technical difficulties.			**•** ^**b**^				
**Evaluation of adherence to hormone therapy treatment by traceability of delivery, adherence notebook and patient declaration**						**•** ^**a**^	**•** ^**a**^
**Return to work and/or daily activities**					**•** ^**b**^	**•** ^**a**^	**•** ^**a**^
**Number of calls to the breast nurse**						**•** ^**a**^	**•** ^**a**^
**Patient satisfaction with 18-month follow-up**							**•** ^**a**^

^a^ During consultation at the Center with the medical oncologist in both arms

^b^ Only for the experimental arm (WEBAPPAC), at home

At inclusion, patients will be asked to complete the following self-questionnaires: EORTC QLQ-C30 and BR23, HADS, and BPI.

During their participation, assessments will be realized 6 and 18 months after the initiation of hormone therapy as follows:

Adherence to hormone therapy (MMAS8, adherence notebook, dispensation, patient report).Quality of life (QLQ-C30 and BR23 self-questionnaires).Anxiety and depression level (HADS self-questionnaire).Return to work and/or daily activities.Pain level (VAS at 6 and 18 months, and BPI at 18 months only).Patient follow-up satisfaction (VAS, at 18 months only).

In addition, patients in the experimental arm will be asked to fulfill the following assessments:

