At 6 weeks and 3 months after the hormone therapy start using the WEBAPPAC web-application:Pain level (VAS).Adherence to hormone therapy (MMAS8).Return to work and/or daily activities, at 3 months only.At 18 months, measurement of the user experience of the web-application via the System Usability Scale (SUS) self-questionnaire.

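### The protocol gives two incompatible procedures for the 6- and 18-month questionnaires in the experimental arm, so collection of a self-reported primary-endpoint component (MMAS8) may differ by arm

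*Protocol article*

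**What the plan says.** **Primary outcome.** The composite rule reads "Adherence failure of hormone therapy will be defined by at least one of the following items". The first of the four items is "Adherence score less than 6 on the 8-item Morisky questionnaire (MMSA8) [22–25], completed at 18 months". The others are a treatment interruption of at least a month in the notebook, a gap of at least a month in dispensation, and permanent discontinuation declared at the 18-month visit.

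**Experimental arm section.** This section describes the experimental arm only: "patients will be reminded (via SMS, and/or email) to complete Patient-Reported Outcomes via the web-application". Two sets of reminder times follow. One is 6 weeks and 3 months after treatment start. The other is "one week before the consultation with the oncologist, planned 6 and 18 months after the hormone therapy start".

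**Study assessments, Table 2.** At 6 and 18 months, MMAS8, QLQ-C30/BR23, HADS and VAS carry footnote a: "During consultation at the Center with the medical oncologist in both arms". So does BPI at 18 months. Footnote b, "Only for the experimental arm (WEBAPPAC), at home", is attached to MMAS8 and VAS at 6 weeks and 3 months, and to the SUS at 18 months. The text after the table agrees with it, placing MMAS8 in the app "At 6 weeks and 3 months after the hormone therapy start using the WEBAPPAC web-application".

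**Control arm section.** It describes consultations at 6 and 18 months. It mentions neither a questionnaire reminder nor completion before the visit.

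**The concern.** One questionnaire cannot be both completed at home in the app a week before the visit and completed during the visit. If the experimental-arm text is what sites follow, the two arms answer the same questions by a different mode, in a different place, on a different date and after different prompting. For most secondary outcomes that would be a nuisance. For MMAS8 it reaches the primary endpoint, because a low score is sufficient for failure whatever the other three items show.

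The 6-month assessment matters too. Under Statistical analyses, 6-month adherence data stand in for patients lost to follow-up at 18 months.

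The trial is open-label and the app is the intervention under test. A difference in how the question was put could therefore not be separated from a difference in adherence.

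**Working it through.** **1. Does the reminder cover MMAS8?** The reminder sentence names no instrument, so this has to be inferred.

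- *6 weeks and 3 months.* The same sentence governs these times. Table 2 schedules MMAS8 and VAS in the app there, so the term used in the sentence includes MMAS8 at those times.
- *6 months.* Every Table 2 entry in this column carries footnote a. No experimental-only item exists to explain an app reminder, which leaves the shared questionnaires as the most plausible target.
- *18 months.* The SUS is an experimental-only, at-home item and could by itself explain a reminder here. But the 6- and 18-month reminders are given in one instruction, and the SUS cannot explain the 6-month half.

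MMAS8 is therefore probably covered, but the text does not say so.

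**2. The plan's own sample size.** Inputs from Sample size determination: 20% v 10%, two-sided alpha 5%, power 80%. With the pooled z-test:

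n = [1.960·√(2·0.15·0.85) + 0.842·√(0.20·0.80 + 0.10·0.90)]² / 0.10² = (0.990 + 0.421)² / 0.01 ≈ 199 per arm, or 398 in total.

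This reproduces the stated figure. Adding 10% gives 199 × 1.10 = 218.9, so 219 per arm. Power at 20% v 10% with 219 per arm is 83.7%.

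**3. What a one-arm shift would do (illustration).** Assume that the collection procedure moves observed composite failure by m points in the experimental arm only. The document gives no value for m. For observed rates p₁ and p₂, with d = p₁ − p₂ and p̄ their mean:

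- s₀ = √(2p̄(1−p̄)/n)
- s₁ = √(p₁(1−p₁)/n + p₂(1−p₂)/n)
- P(reject) = Φ((d − 1.96 s₀)/s₁) + Φ((−d − 1.96 s₀)/s₁)

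*No true effect, m = 3, failure under-reported (20% v 17%, n = 219).* s₀ = 0.03711 and s₁ = 0.03708. P = Φ(−1.152) + Φ(−2.770) = 0.125 + 0.003 = 0.127.

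*True 20% v 10%, m = 3, failure over-reported (20% v 13%).* s₀ = 0.03547 and s₁ = 0.03531. P ≈ Φ(0.013) = 0.505.

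| Assumed m (points) | False-positive rate, true 20% v 20%, failure under-reported | Power, true 20% v 10%, failure over-reported |
|---|---|---|
| 0 | 5% | 83.7% |
| 1 | 5.8% | 74% |
| 2 | 8.3% | 63% |
| 3 | 12.7% | 51% |
| 5 | 28.0% | 28% |

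With 199 per arm, the false-positive rates for m = 2, 3 and 5 are 8.0%, 12.0% and 25.9%.

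**4. What m means here.** A 3-point shift in the composite is 0.03 × 219 ≈ 6.6 patients in one arm. Only patients for whom MMAS8 decides the outcome, with none of the other three items failing, can move. The shift in MMAS8 classification itself would have to be at least as large as m.

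**The case against.** The strongest reply is that wherever the article schedules MMAS8 by name, collection at 6 and 18 months is equal: Table 2 and the text after it agree. If Table 2 governs, mode does not differ by arm and the reminder sentence is only loosely worded. The app also invites periodic symptom reports that are not a Table 2 row, and these could be what the 6-month reminder means. This stands in part. It rules out stating as fact that the 18-month MMAS8 is collected by app. It does not remove the conflict, because the symptom notifications are described separately with their own schedule, and nothing in the article says which passage prevails.

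It is also fair that silence about control-arm reminders does not prove there are none, since a condensed article may omit such logistics. And three of the four failure items do not depend on the app, which dilutes any effect.

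A reader might infer three stronger points that the document does not support:

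- *That a poor answer has consequences in one arm only.* The app's functions do include "Alerting the nurse accompanying the patient on the breast cancer treatment pathway in the event of non-adherence with the hormone therapy treatment". But the article does not say that an MMAS8 answer triggers this alert, and Secondary outcomes compares warnings to nurse or oncologist, and appointments for low adherence, between both arms.
- *That one-arm reminders create unequal missing data which the imputation rule turns into outcomes.* That rule concerns patients lost to follow-up at 18 months, not attenders with a missing questionnaire.
- *That the bias favours the app.* Answering at home rather than at the oncologist's visit could equally raise reported failure.

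**Conclusion.** The point holds as a conflict between two stated procedures, with a conditional risk to the primary comparison. If the experimental-arm text is followed and its reminder includes MMAS8, which is the most plausible reading, then mode, place, timing and prompting of a self-reported endpoint component may differ by arm. If Table 2 is followed, they do not, and only the wording needs correcting.

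Neither the size nor the direction of any bias can be determined from the document. The 3-point illustration (false-positive rate of about 13%, or power of about 51%) shows only that a shift of about seven patients in one arm would matter. It assumes 219 analysed per arm and a shift in the whole composite. The correction is worth making because it is cheap and removes the ambiguity from the primary endpoint.

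**What to change.** Reconcile the experimental-arm section with Table 2. At 6 and 18 months, have both arms complete MMAS8, QLQ-C30/BR23, HADS and VAS (and BPI at 18 months) on the same form, at the same time relative to the visit, with the same reminder and outside the app. Keep the 6-week and 3-month app questionnaires and the SUS as experimental-arm items, and reword the reminder sentence to match.

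The cost is a change to the app schedule and site instructions, with no extra visits or patients. The downside is that experimental patients answer the 6- and 18-month questionnaires outside the app. If some have already answered by app, a change would mix modes within that arm, so the mode used should be recorded for each assessment.

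A supportive analysis of the dispensation criterion alone, which Table 2 schedules alike in both arms, is optional.

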### Study assessments

The overview of study assessments and procedures is detailed in Table 2.

**Table 2 Tab2:** Overview of study assessments in the WEBAPPAC study

TIME Point	Before inclusion	Inclusion and randomisation ^a^	Day 15^b^	6 Week^b^	3-months^b^	6-months^a^	18-months ^a^
		Visit 1				Visit 2	Visit 3
Informed consent	•	•^a^					
**Training of the patient in the Web application**		**•** ^**b**^					
**Medical examination** (medical history, weight, height, vital parameters)		**•** ^**a**^					
**Quality of life self-report questionnaires (EORTC QLQ C30; and QLQ BR23)**		**•** ^**a**^				**•** ^**a**^	**•** ^**a**^
**Anxiety and Depression Questionnaire (HADS)**		**•** ^**a**^				**•** ^**a**^	**•** ^**a**^
**Assessment of pain using the Visual Analogue Scale (VAS)**				**•** ^**b**^	**•** ^**b**^	**•** ^**a**^	**•** ^**a**^
**Pain score (BPI)**		**•** ^**a**^					**•** ^**a**^
**Morisky Medication Adherence Scale (MMAS8)**				**•** ^**b**^	**•** ^**b**^	**•** ^**a**^	**•** ^**a**^
**Measurement of user experience (self-questionnaire (SUS))**							**•** ^**b**^
**Phone call** to ensure that there are no technical difficulties.			**•** ^**b**^				
**Evaluation of adherence to hormone therapy treatment by traceability of delivery, adherence notebook and patient declaration**						**•** ^**a**^	**•** ^**a**^
**Return to work and/or daily activities**					**•** ^**b**^	**•** ^**a**^	**•** ^**a**^
**Number of calls to the breast nurse**						**•** ^**a**^	**•** ^**a**^
**Patient satisfaction with 18-month follow-up**							**•** ^**a**^

^a^ During consultation at the Center with the medical oncologist in both arms

^b^ Only for the experimental arm (WEBAPPAC), at home

At inclusion, patients will be asked to complete the following self-questionnaires: EORTC QLQ-C30 and BR23, HADS, and BPI.

During their participation, assessments will be realized 6 and 18 months after the initiation of hormone therapy as follows:

Adherence to hormone therapy (MMAS8, adherence notebook, dispensation, patient report).Quality of life (QLQ-C30 and BR23 self-questionnaires).Anxiety and depression level (HADS self-questionnaire).Return to work and/or daily activities.Pain level (VAS at 6 and 18 months, and BPI at 18 months only).Patient follow-up satisfaction (VAS, at 18 months only).

In addition, patients in the experimental arm will be asked to fulfill the following assessments:

At 6 weeks and 3 months after the hormone therapy start using the WEBAPPAC web-application:Pain level (VAS).Adherence to hormone therapy (MMAS8).Return to work and/or daily activities, at 3 months only.At 18 months, measurement of the user experience of the web-application via the System Usability Scale (SUS) self-questionnaire.

### Assessment tools

#### Adherence to hormone therapy

Initially developed for patients undergoing antihypertensive treatment, the Morisky Medication Adherence Scale-8 is widely used to assess adherence to oral treatments, particularly hormone therapy. The MMAS-8 is the most recent version of the questionnaire developed by the Morisky team [22–25]. It contains 8 items, with binary choice for the first 7 ones and with 5-Likert scale for the 8th question.

The total score ranges from 0 to 8 points: a score < 6, between 6 and < 8, and of 8 points reflects respectively a low, medium and high adherence. The questionnaire will be proposed in its French validated form [26].

#### Quality of life

Quality of life will be assessed using the European Organization for Research and Treatment of Cancer (EORTC) QLQ-C30 (Quality of Life Questionnaire-Core 30 items) self-administered questionnaire exploring general dimensions of quality of life (30 items) [26], and its add-on Breast module (BR23, 23 items) for breast cancer [27].

The EORTC QLQ-C30 questionnaire measures functional status (physical, social, emotional, cognitive), symptoms (fatigue, pain, nausea and vomiting), quality of life and health status, as well as cancer symptoms and common side effects of cancer therapy (such as loss of appetite) [26]. The self-administered BR23 module explores more spherically the quality of life of patients managed for breast cancer through [27]:

o 4 functional dimensions: body image (measures felt body image, due to the disease such as body perception, femininity, her view of her naked image), sexuality (interest), future perspective (health anxiety in the future),

o 4 symptom dimensions: treatment side effects (adverse drug reactions such as hot flashes, headaches, etc.), breast symptoms (pain, skin condition in the treatment area, sensitivity), arm symptoms (painful arm, increase in volume, difficulty mobilizing), hair loss.

#### Anxiety/depression

The patients’ anxiety and depression levels will be assessed using the “Hospital and Depression Scale (HADS)” [28]. It is composed of 14 items: 7 items assessing depression and 7 items assessing anxiety, providing both anxiety and depression scores. The highest scores correspond to the presence of more severe symptoms. HADS will be provided in its French validated form [29].

#### Pain

Assessment of pain intensity will be based on the use of the Visual Analogue Scale (VAS), widely used in clinical routine. Furthermore, pain and its impact on the patient’s daily life will be assessed using the French validated form of the Brief Pain Inventory (BPI) [30], in its short version, validated for assessing pain in cancerology and recommended by the French High Authority of Health (HAS) [31]. The BPI allows assessment of intensity and location of the pain, as well as its treatment and the way it is relieved. Pain intensity is rated from 0 to 10 according four components: maximum pain, minimum pain, average pain and current pain. Item 9 of the short version of the BPI also allows to assess the impact of pain on daily activities, by considering 2 sub-dimensions (affect and activity). This subscale, recommended by the French HAS to assess the patient’s “quality of life”, explores the impact of pain on general activity, mood, ability to walk, usual work, relationship with others, sleep and taste for life. Each item is scored by the patient between 0 (no discomfort) and 10 (complete discomfort).

The user experience with the WEBAPPAC web-application will be assessed using the System Usability Scale (SUS) questionnaire [32–34]. This questionnaire composed of 10 questions allows determining the level of satisfaction of the users as concerning a service (a software, an application). It measures experience of patients and professionals with the web-application by evaluating the “usability” or “friendliness” of the service.

